### Design

This study is a randomized, assessor-blinded, multicenter, clinical trial with two parallel groups. We intend to investigate the synergic effects of Palmijihwang-hwan with acupuncture treatment in patients with CLBP. Eligible participants will be assigned to one of two groups, the control group (only acupuncture) or the treatment group (Palmijihwang-hwan + acupuncture). The flowchart is as shown in Fig. 1. The Standard Protocol Items: Recommendations for Interventional Trials (SPIRIT) checklist is provided in Additional file 1.

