### Procedure

The study schedule is as shown in Fig. 2. At the screening visit, patients who are interested in participation and who visit one of the four Korean medicine hospitals will be informed about the study. They will be also informed about expected benefits and risks and that they are able to withdraw from the study at any visit. If they sign the informed consent form voluntarily, the investigator will perform several examinations including check of vital signs, physical examination, spine x-ray, blood chemistry test, pregnancy test, and will collect demographic data, CLBP history, and concomitant treatment data, and apply the VAS, to determine the patient’s eligibility. If patients are eligible for the study but are taking medication, the investigator will determine the day of screening according to the participant’s medication to give a washout period. If the participant is taking anti-inflammatory medication or painkillers, the investigator will give a 2-week washout period. During the 6-week treatment, the participants in both groups will visit the hospital twice a week (total 12 visits) and receive acupuncture treatment at every visit. Participants in the treatment group will additionally receive Palmijihwang-hwan (at visit 1, 4, and 8) during the treatment period. Then, participants in both groups will be asked to complete a survey every 2 weeks (at visit 4, 8, and 12). On visit 13, 4 weeks after visit 12, all participants will visit the hospital for the final time.

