### Safety assessment

Physical examinations will be performed at the screening visit and at visit 1 and 13. Blood chemistry tests including pregnancy tests will be conducted at the screening visit and visit 12. The blood chemistry test will assess the red blood cell (RBC) count, white blood cell (WBC) count, hemoglobin (Hb), hematocrit (Hct), platelet count, erythrocyte sedimentation rate (ESR), aspartate aminotransferase (AST), alanine aminotransferase (ALT), blood urea nitrogen (BUN), creatinine, electrolytes (Na, K, Cl), and C-reactive protein (CRP). Vital signs, adverse events, and change in medication/treatment will be checked at every visit.

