### Statistical analysis

Continuous variables at baseline will be expressed as means plus/minus standard deviation and statistically tested using the two-sample *t* test or the Wilcoxon rank sum test. Categorical variables at baseline will be expressed as frequencies and statistically tested using the chi-squared test or Fisher’s exact test. If there is a significant difference between groups, the baseline variable will be considered as a covariate for efficacy analysis.

The full analysis set (FAS) will be analyzed primarily, including participants who take at least one dose of Palmijihwang-hwan and complete at least one pain assessment. Also, the per-protocol set (PPS) will be subordinately analyzed, including participants who take more than 80% of the total Palmijihwang-hwan dose and complete the trial. In the FAS analysis, the missing data will be imputed using the method of last observation carried forward. The primary outcome (change in the VAS score between baseline and endpoint) will be tested by analysis of covariance (ANCOVA) or rank ANCOVA (according to normality or homoscedasticity) with factors of group and study site and covariates of baseline values. Continuous variables for the secondary outcomes will also be tested, respectively, by ANCOVA or rank ANCOVA. Categorical variables for the secondary outcomes will be tested by chi-squared test or Fisher’s exact test according to the number of the cells with a value of 5 or less in the contingency table. Every variable predefined in the outcome sections will be compared at each time point, respectively.

The safety set will include participants who receive at least one dose of Palmijihwang-hwan. In safety analysis, the frequency and ratio of adverse events will be applied and compared between the treatment group and the control group using the chi-squared test or Fisher’s exact test. Any abnormal change in blood chemistry tests from visit 1 to 12 will be expressed as frequency and percentage and compared between the treatment group and the control group using McNemar’s chi-squared test, and any change in vital signs between visit 1 and 12 and between visit 1 and 13 will be expressed as change scores and compared between the treatment group and the control group using the two-sample *t* test or the Wilcoxon rank-sum test. Statistical tests will be carried out at 5% significance level (two-sided), using R software (Version 3.5.0 or later; R Foundation for Statistical Computing, Vienna, Austria).

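### Abnormal blood chemistry changes are to be compared between two independent arms with McNemar's paired test, from a visit 1 baseline at which the text schedules no blood sample

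*Protocol article*

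**What the plan says.** The design is stated plainly in the Design section: "This study is a randomized, assessor-blinded, multicenter, clinical trial with two parallel groups". The Participants section adds 1:1 random assignment and mentions no matching.

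The safety paragraph of the Statistical analysis section sets out three between-arm comparisons:

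- **Adverse events:** frequencies compared by chi-squared or Fisher's exact test.
- **Laboratory values:** "Any abnormal change in blood chemistry tests from visit 1 to 12 will be expressed as frequency and percentage", and then "compared between the treatment group and the control group using McNemar’s chi-squared test".
- **Vital signs:** change scores compared by the two-sample t test or the Wilcoxon rank-sum test.

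The same paragraph defines the safety set as participants who have had one or more doses of Palmijihwang-hwan.

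On the timing of blood samples, the Safety assessment section says: "Blood chemistry tests including pregnancy tests will be conducted at the screening visit and visit 12".

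**The concern.** McNemar's test uses the discordant members of matched pairs. In this trial the only natural pairing is a participant with himself or herself at two times, so the test can ask whether shifts to abnormal outnumber shifts back to normal within one arm. Nobody in the treatment arm is paired with anybody in the control arm, so it cannot ask whether the arms differ.

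An analyst who follows the sentence therefore has two choices. One is to find no pairs and be unable to proceed. The other is to run the test once per arm and set two p-values side by side. The second choice leaves the trial without the between-arm laboratory comparison that the sentence promises, and it invites the reader to treat a difference in significance as a difference between arms.

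The baseline is a second, smaller problem. The change is counted from visit 1, a visit at which the text schedules no blood chemistry.

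What is at stake is one part of the safety evidence. Safety is a stated objective, and the Discussion says the safety assessment may inform on the toxicity of the aconite ingredient.

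**Working it through.** **1. Which data structure does the sentence describe?**

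| Comparison (Statistical analysis, safety) | Outcome type | Groups compared | Test named | Fits independent arms? |
|---|---|---|---|---|
| Adverse events | binary | treatment v control | chi-squared or Fisher | yes |
| Abnormal laboratory change | binary | treatment v control | McNemar | no |
| Vital-sign change | continuous | treatment v control | two-sample t or Wilcoxon rank-sum | yes |

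The adverse-event and laboratory rows have the same structure and get different tests. The laboratory row is the only one with a paired test.

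**2. Is there a visit 1 blood sample?**

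- Procedure lists among the screening examinations "spine x-ray, blood chemistry test, pregnancy test".
- Safety assessment places blood chemistry at screening and visit 12.
- The sentence just before that one reads "Physical examinations will be performed at the screening visit and at visit 1 and 13", so screening and visit 1 are different visits in the article's own usage.

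On the text, the available pair of samples is screening and visit 12, not visit 1 and visit 12. The schedule figure (Fig. 2) is not shown and could not be checked.

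**3. What could the named test produce?**

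The article gives no expected abnormality rates, so these counts are assumed for illustration. The arm size of 42 is from the Sample size calculation section. Let 6 treatment and 5 control participants move from normal to abnormal, and none move back.

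McNemar's chi-squared with continuity correction is (|b − c| − 1)² / (b + c), where b and c are the two kinds of discordant change, on 1 degree of freedom.

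- Treatment arm: (6 − 1)² / 6 = 4.17, p = 0.041.
- Control arm: (5 − 1)² / 5 = 3.20, p = 0.074.

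Between arms, 6/42 v 5/42:

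- Fisher's exact test: p = 1.0.
- Risk difference: 0.143 − 0.119 = 0.024.
- Standard error: √(0.143 × 0.857/42 + 0.119 × 0.881/42) = 0.074.
- Approximate 95% CI: 0.024 ± 1.96 × 0.074, about −0.12 to 0.17.

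**4. How sensitive is the illustration?**

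| McNemar variant | Treatment (6 v 0) | Control (5 v 0) |
|---|---|---|
| Chi-squared, continuity-corrected | 0.041 | 0.074 |
| Chi-squared, uncorrected (6²/6 = 6; 5²/5 = 5) | 0.014 | 0.025 |
| Exact binomial (2 × 0.5⁶; 2 × 0.5⁵) | 0.031 | 0.063 |

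The split across 0.05 appears with the corrected and exact forms and disappears with the uncorrected form. Under every variant, neither p-value compares the arms.

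The number of participants per arm does not enter the McNemar calculation. Fisher's p also stays at 1.0 for any equal arm sizes, because 6 v 5 and 5 v 6 are then the two most likely splits of 11 events. Losing participants equally to the assumed 20% dropout therefore does not change the example.

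**5. Can the corrected test be run on the safety set as defined?**

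Control participants receive acupuncture only. Read literally, a safety set that requires a dose of Palmijihwang-hwan contains no controls, so no between-arm safety test can be run on it.

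**The case against.** The best defence is that the authors meant a within-person shift analysis, for which McNemar's test is a legitimate choice, and worded it loosely. That may be so, but the sentence names a comparison between the two groups. The within-arm reading would leave that comparison untested. An analysis plan that is not shown does not cure this, because the article states the test outright.

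Several limiting points stand:

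- The clause belongs to the safety analysis. Frequencies and percentages will be reported whichever test is used, adverse events get a suitable test, and the Adverse events section also has abnormal blood chemistry changes checked.
- A reader might infer that the laboratory results are the trial's principal safety evidence. The article does not rank them. It refers to the safety assessment as a whole, which also covers physical examination, vital signs, adverse events and medication changes.
- A reader might infer that no baseline exists. A pre-treatment sample is taken at screening, so the likeliest explanation is a slip in naming the visit. Procedure does say "the investigator will give a 2-week washout period" to users of anti-inflammatory drugs or painkillers. But it ties the day of screening to that washout, which may come before screening, so no material gap between screening and visit 1 is shown.
- A reader might force McNemar's test onto the arm-by-abnormality table and conclude that false signals are almost certain. For example, 4/42 abnormal in each arm would give (|38 − 4| − 1)² / 42 = 25.9, p = 3.5 × 10⁻⁷. The article describes no such calculation, so this does not estimate the error the trial would make.

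**Conclusion.** The sentence is wrong as written and should be fixed. A paired test is assigned to a comparison of two independent groups, while the same paragraph uses suitable tests for the other two safety comparisons. This conclusion needs no assumption beyond the stated parallel-group design.

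The baseline wording is a lesser inconsistency between sections. It rests on the text alone and is subject to Fig. 2.

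The numerical example shows how within-arm p-values can mislead. Its counts are assumed, and the contrast depends on the variant of the test, so it does not measure expected harm. Nothing here touches the primary analysis or the sample size, and a reading that the trial's safety conclusions as a whole are invalid would go beyond the document.

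**What to change.** 1. Replace McNemar's test for the between-arm comparison. Compare the proportion of participants with a new abnormal change from screening to visit 12 by chi-squared or Fisher's exact test, as is already planned for adverse events. Report a risk difference with its 95% CI.
2. Add shift tables by arm. They should also show worsening of values that were already abnormal, which a count of new abnormalities would miss.
3. If McNemar's test is kept, label it as a within-arm description and draw no between-arm conclusion from it.
4. Reconcile the laboratory baseline between the Statistical analysis and Safety assessment sections by naming the screening sample, after checking Fig. 2.
5. Reword the safety set so that it includes control participants. Without this, item 1 cannot be carried out.

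The cost is wording in the protocol or analysis plan. No extra samples, participants or change to the sample size are needed.

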### Sample size calculation

We performed sample size calculations to determine the appropriate number of participants. The purpose of this study is to verify the synergic effect of the combination treatment (acupuncture + Palmijihwang-hwan) compared to acupuncture treatment alone, using a visual analog scale (VAS) score for change between baseline and completion of the intervention (6 weeks). However, no study has been conducted to investigate the effects of Palmijihwang-hwan combined with acupuncture in the treatment of CLBP. Thus, we reviewed a similar study conducted in patients with CLBP [27] in which the authors evaluated the efficacy of a herbal formula, Ojeok-san, by measuring the VAS score change between baseline and completion of the intervention (4 weeks) and comparing this with the placebo group in randomized clinical trials of CLBP. In that study, the change in VAS score between baseline and completion of the intervention was − 26.41 ± 19.06 in the treatment group and − 12.83 ± 19.45 in the control group. Based on these data, 33 participants would be required per intervention group for a two-arm study and a two-tailed test with 0.80 power (1-β) at the 0.05 α level, as calculated using G* Power (Version 3.1.9.3) [28]. After assuming a 20% drop out rate, we calculated that we would need to recruit 42 participants per group. Thus, a total of 84 participants will be required.

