### Randomization and allocation concealment

A randomization sequence will be generated by an independent statistician who does not participate in this study, using R software (Version 3.5.0; R Foundation for Statistical Computing, Vienna, Austria). Randomization will be stratified based on four Korean medicine hospitals, and then block randomization will be used to approximately equalize the number of participants in each group. A random code will be delivered in the sealed envelopes, in which the allocated group is written. A delegated investigator in each site will open the envelope in sequence and allocate a participant to either intervention or control arm, only when all the screening criteria are satisfied. Allocation will be concealed until the investigator opens each sealed envelope. The randomization sequence will be kept by the independent statistician or physician during the clinical trial period and concealed until the occurrence of the event predefined as a reason for code-breaking.

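### Vital-sign changes are compared without adjusting for baseline or site; the test is valid, but ANCOVA, already used for the primary outcome, would be more precise at no cost

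*Protocol article*

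**What the plan says.** All of the following is in the protocol article.

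- **Vital signs (Statistical analysis, safety paragraph).** Changes from visit 1 to 12 and from visit 1 to 13 "will be expressed as change scores and compared between the treatment group and the control group using the two-sample" (Student's t test is meant, with Wilcoxon's rank-sum test as the alternative). No baseline or site term is named.
- **Primary outcome (same section, preceding paragraph).** Change in VAS is tested by ANCOVA or rank ANCOVA "with factors of group and study site and covariates of baseline values". Continuous secondary outcomes also get ANCOVA or rank ANCOVA.
- **Baseline imbalance (same section, first paragraph).** A baseline variable that differs significantly between groups becomes a covariate, but only for the efficacy analysis.
- **Randomisation.** "Randomization will be stratified based on four Korean medicine hospitals".
- **Data available (Safety assessment).** Vital signs are recorded at every visit, so the visit 1 value exists.

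**The concern.** Two change-from-baseline comparisons in one section are handled differently, and no reason is given. Safety is a stated objective, the product contains processed *Aconitum carmichaelii*, and the Discussion expects the safety assessment to inform on its toxicity. Adverse events and blood chemistry are compared as frequencies, so vital signs are the only safety comparison specified on a continuous scale.

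A change score subtracts the whole baseline value. This fixes the baseline slope at 1, whereas ANCOVA estimates it. When the correlation between baseline and follow-up is well below 1, the change score carries avoidable noise, and a real shift is somewhat less likely to be seen. In a safety comparison, lost precision makes it easier to conclude that nothing differed.

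**Working it through.** **1. The plan's own figure.** Sample size calculation takes changes of minus "26.41 ± 19.06 in the treatment group" and minus "12.83 ± 19.45 in the control group", for "a two-tailed test with 0.80 power (1-β) at the 0.05 α level".

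- Difference: 26.41 − 12.83 = 13.58.
- Pooled SD: √((19.06² + 19.45²)/2) = 19.256, so d = 13.58/19.256 = 0.705.
- A two-sample t test (noncentral t) needs 33 per arm (power 0.806). This matches the statement that "33 participants would be required per intervention group".
- With 20% dropout: 33/0.8 = 41.25, rounded up to 42 per arm, 84 in total. The figure reproduces.

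This calculation concerns VAS only; nothing is powered on vital signs. For a comparison at visits 12 and 13, the last two visits, the planned evaluable number is 33 per arm; 42 is the number randomised.

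**2. Variance of the two estimators.** With equal variances SD² at both visits and correlation rho:

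- change score: 2(1 − rho)SD²
- baseline-adjusted ANCOVA: (1 − rho²)SD²
- ratio: (1 − rho²)/(2(1 − rho)) = (1 + rho)/2

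**3. Power for an illustrative shift.** Assumed, because the documents give none of these: true shift 5 mmHg, SD 12, rho 0.3 to 0.9. Two-sided 5%, 33 per arm. The SDs are 12√(2(1 − rho)) and 12√(1 − rho²). At rho 0.5 they are 12.00 and 10.39.

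The ANCOVA power is given twice:

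- (a) charging only baseline: 63 degrees of freedom, variance × (1 + 1/62)
- (b) charging baseline and three site terms: 60 degrees of freedom, variance × (1 + 4/59), with site assumed to explain nothing

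The change-score test has 64 degrees of freedom.

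| rho | variance ratio | power, change score | ANCOVA (a) | ANCOVA (b) |
|---|---|---|---|---|
| 0.3 | 0.65 | 29% | 41% | 39% |
| 0.5 | 0.75 | 39% | 48% | 46% |
| 0.7 | 0.85 | 58% | 64% | 62% |
| 0.8 | 0.90 | 75% | 79% | 77% |
| 0.9 | 0.95 | 96% | 97% | 96% |

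**4. Interval width.** The 95% confidence interval half-width in SD units at 33 per arm, change score against ANCOVA (b):

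- rho 0.5: 0.492 against 0.441
- rho 0.7: 0.381 against 0.363
- rho 0.9: 0.220 against 0.222

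The interval narrows by about 10% at rho 0.5 (0.441/0.492 = 0.90) and about 5% at rho 0.7 (0.363/0.381 = 0.95). At rho 0.9 it is marginally wider.

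**The case against.** The strongest reply is that nothing here is wrong. Four parts of it stand.

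- **Validity.** In a 1:1 randomised trial the t or Wilcoxon test on change scores controls type I error, and the mean difference is unbiased. Leaving out a stratification factor usually makes the test slightly conservative.
- **Purpose.** Vital signs are neither a primary nor a listed secondary outcome. No hypothesis, margin or decision is attached to them, and unadjusted safety comparisons are conventional. Treating safety more simply than efficacy is not a contradiction.
- **Size.** The gain depends on a correlation that the documents do not give, and it vanishes near 0.9.
- **Adequacy.** Power in the example stays low at rho 0.5 whichever method is used, so adjustment does not make this a well-powered comparison.

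Three stronger readings are tempting but unsupported. A reader might infer that regression to the mean biases the estimated herb effect. That is true only conditional on a chance baseline imbalance; over randomisation the imbalance averages zero and is already in the standard error, so it is the same precision argument restated. A reader might infer that ignoring site costs power, but nothing in the documents shows that site explains vital-sign variance. A reader might also work with 42 per arm and charge nothing for the covariates, which gives 47% against 59% at rho 0.5. Those figures are arithmetically right but use the number randomised, before the planned dropout.

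The reply does not remove the point that a more precise method, already in the plan and needing no new data, is available.

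**Conclusion.** The point holds as a minor, free improvement. The planned vital-sign comparison is sound but less precise than the model used for the primary outcome. The variance is 5% to 35% lower with baseline adjustment for rho from 0.9 down to 0.3, before degrees of freedom are charged. In the illustration with 33 per arm, the gain is roughly 8 to 9 percentage points of power at rho 0.5, 4 to 6 at rho 0.7, and practically nil at rho 0.9. These figures rest on an assumed SD, shift and correlation and on equal variances at the two visits; only the ratio (1+rho)/2 is free of the SD and shift. The case for including site is consistency with the stratified design and the primary model, not a demonstrated gain. No conclusion about the primary outcome depends on this.

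A separate and more serious matter affects the same comparison. The safety set is defined by receipt of at least one dose of Palmijihwang-hwan, which the control group does not receive. Read literally, there is no control arm to compare, with or without covariates.

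**What to change.** In the safety paragraph of Statistical analysis, replace the two-sample t test or Wilcoxon test for vital-sign change by ANCOVA with group, study site and the visit 1 value, or rank ANCOVA if the normality or variance assumptions fail. Report the adjusted group difference with its 95% confidence interval for each of the two intervals (visit 1 to 12, visit 1 to 13).

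Define the safety set so that it also includes control participants; otherwise this comparison cannot be made.

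The cost is one or two sentences of analysis wording. No extra data, visits or participants are needed. The only statistical price is four degrees of freedom, which matters only if the correlation is very high.
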